### **5.2.2 Randomization**

Treatment intervention will be randomly allocated to patients with active TB when patients enter Step 2 of the study. Eligible TB patients will be randomized with an allocation ratio of 1:1 to receive either punctuated ARV therapy or anti-TB treatment only with delayed ARV therapy. Randomization will be done with a permuted-block size of 16 to reduce the likelihood of unbalanced study arms in terms of size and prognostic factors. The assignment to study arm will be made by the UCSF data center to reduce the likelihood of inappropriate enrollment or treatment allocation.

Before the trial begins a list of computer-based random numbers will be generated using a pseudo-random number generator. These randomly allocated numbers will be used to assign eligible study patients to study arm. This list will be retained at the data center at UCSF. Once eligibility for study entry into Step 1 has been determined through the screening process, a form that contains a summary of study entry inclusion and exclusion criteria will be sent to the statistical center. Patients enter Step 1 where they are started on anti-TB treatment and monitored for contraindications to start the Trizivir-based ARV intervention regimen. All patients will be assessed beginning at week 1 and up to week 3 for contraindications to starting intervention. Upon determination of eligibility criteria for randomization, a form with criteria for randomization will be sent to the UCSF data center. Study entry and randomization criteria will be verified and a treatment assignment made according to the list of random numbers. Upon randomization, patients enter Step 2 of the study where they are initiated into study arm. Patients with contraindications for starting Trizivir-based punctuated ARV therapy without resolution during the 2 to 4 week period will be registered to Step 2, will not be randomized, will not be included in the primary analysis of the study, but will remain on study follow-up. They will be eligible for entry into Step 3 of the study, if during the study period, their CD4+ count drops 250/ml or an AIDS- defining condition develops as defined by WHO stage IV HIV infections or a definitive diagnosis of a severe bacterial infection that meets WHO Stage 3 classification (Appendix II).

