### **6.3.2 Development of ARV drug resistance**

Viral drug resistance will be examined in specimens from patients with confirmed failure to suppress HIV RNA < 200 copies/ml after the six month course of antiretroviral therapy on step 2 or after six months of antiretroviral therapy on Step 3, and, for a random subset of 20 patients 2 months after completing punctuated therapy. In these patients, pre-treatment plasma will also be assayed for drug resistance. Genotypic analysis performed at the Joint Clinical Research Center Virology laboratory will be used to evaluate for drug resistance. Resistance will be defined according to IAS/USA guidelines.

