# 10.0 STATISTICAL CONSIDERATIONS

## 10.1 Sample Size

In this randomized clinical trial we will enroll a total sample size of 350 HIV-infected TB patients into Step 2 with 175 randomized to punctuated therapy and 175 randomized to anti-TB treatment only and delayed ARV therapy. The sample size was estimated to provide a power of 80 – 90% to detect an effect size of 35% or greater for HIV disease progression. This effect size translates into an average delay of about one year before the need to start ARV therapy. The sample size will not include patients who enter Step 1 but are not eligible to progress to Step 2.

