**Figure 5. Sample Size Calculation**

Power of designed study according to sample size per arm and effect size. Assumptions in calculations: alpha=0.05 (2 tailed), 1600 simulations, 95% confidence intervals for estimated proportions, a 3-year accrual period, and 5% dropout per year, constant hazard throughout period, and Cox Mantel-Haenszel test statistic for the comparison of two survival distributions.74 (A.) 50% disease progression by 2 years in reference group; (B.) 50% disease progression by 3 years in reference group, i.e., slower disease progression than expected. The simulations were implemented using N QueryAdvisor.75

Under the assumption that 50% of patients in the reference group will progress to CD4+ count < 250/µL within 2 years and an effect size of 35%, a power of 80% would be achieved with 125 TB patients per arm, and 90% with 175 patients per arm. Under the assumption that 50% of patients in the reference group will progress to CD4+ count < 250 within 3 years and an effect size of 35%, a power of 80% would be achieved with 175 subject per arm, and 90% with 250 subjects per arm. Based on this analysis, we chose a sample size of 175 TB patients per arm for a total of 350 TB patients. The sample size of 350 TB patients also ensures a large enough sample size to examine secondary outcomes with power of 80% or greater in each comparison.

Figure 5.

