#### **10.2.2.2 Specific Aim 2**

To determine whether a punctuated six-month course of ARV therapy during treatment of active TB will improve the response to antituberculous therapy, as measured by one month culture conversion, treatment failure, and relapse TB, among patients with active TB and CD4+ cell count above 350 cells/µL.

The analysis of this Specific Aim will include only patients with active TB that have been randomized in the clinical trial. The effect of ARV treatment on the response to antituberculous therapy will be evaluated by comparing the proportion of subjects with negative smears or cultures at one and two months (chi square test). A similar analysis will be performed for antituberculosis treatment failure in the ARV treatment arms compared to the reference arm.

Previous published studies of TB in HIV infection estimate relapse rates between 3 and 10%; we thus expect to identify between 10 to 35 relapse cases of TB during the study. The cumulative incidence of TB relapse will be estimated by group using Kaplan-Meier methods; incidence density methods will also be used to measure the number of relapses per 100 person-years of observation after completing antituberculous treatment according to ARV treatment group. The incidence density ratio (95% confidence interval) will be estimated to compare incidence in treated and reference groups. Cox regression analysis will be used to determine whether punctuated ARV therapy is associated with relapse after adjusting for covariates. The analysis will account for the different treatment histories by using time-dependent Cox proportional hazards analysis. The analysis will be further stratified according to relapses due to reactivation and reinfection based on the RFLP patterns.

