4. Compare the results of CD4, HIV RNA viral load and anti-retroviral resistance testing from dried blood spot testing to those found using traditional venipuncture methods.

Patient population for virology sub-analyses:

Patients enrolled in the PART study at the TBRU in Kampala, Uganda will be included in these analyses. These patients are recruited from the National TB and Leprosy Program (NTLP) clinic in Kampala.

Analytic Design:

For this prospective nested sub-analysis of PART one additional blood draw will be scheduled to answer questions related to viral dynamics, viral subtypes, and anti-retroviral resistance. Additional virology and immunologic assays will be performed on banked serum and plasma specimens obtained during routine blood draws as outlined in the PART protocol.

In addition to the currently scheduled tests at baseline (HIV RNA and CD4 lymphocyte count), we will determine baseline HIV DNA, HIV genotype, HIV viral subtype, HIV co-receptor, presence of dual infection, and markers of immune activation (CD38+, DR+). We propose the addition of a plasma HIV RNA level at day 7 and day 14, and the addition of a CD4 lymphocyte count level at day 14 and day 28 (month 1) of the study intervention phase. At six months, testing to determine HIV subtype and presence of dual infection or recombinant variants, HIV DNA and RNA load, as well as antiretroviral resistance testing will be repeated in all patients. For patients randomized to receive immediate ART, repeat antiretroviral resistance testing will also be scheduled at the time of first positive VL specimen after discontinuation of ART at six months.

Viral decay after initiation and discontinuation of ARV will be analyzed assuming biphasic exponential decay characteristics. Comparisons of decay rates will be made using non-p

arametric methods (paired or unpaired Wilcoxon test). Clinical measurements of immune activation and viral RNA and DNA load, as well as baseline CD4+ lymphocyte count and markers of viral subtype and baseline resistance will be fitted in a multivariate regression model to determine independent predictors of first and second phase viral decay rates.

The presence of anti-retroviral resistance will be determined by standard sequencing methods. To determine independent predictors of resistance mutations, measurements of viral dynamics, including HIV RNA and DNA, and viral decay rates, as well as viral subtype will be analyzed in a multivariate model.

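### Section 10.1 promises at least 80% power in every secondary comparison, but on the protocol's own event counts this does not hold for TB relapse

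*Protocol*

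**What the plan says.** Section 10.1 sizes the trial on the primary outcome: "175 randomized to punctuated therapy and 175 randomized to anti-TB treatment only", for a "power of 80 – 90% to detect an effect size of 35% or greater for HIV disease progression". After the two primary scenarios, the text accompanying Figure 5 adds that the same total provides a "large enough sample size to examine secondary outcomes with power of 80% or greater in each comparison". Nothing further is given for the secondary outcomes.

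TB relapse is a named secondary outcome (Synopsis, Section 2.2 and Table 6). Section 10.2.2.2 takes a relapse rate of 3 to 10% from published studies and concludes: "we thus expect to identify between 10 to 35 relapse cases of TB during the study". It then plans a between-arm comparison by incidence density ratio and Cox regression, with a further split into reactivation and reinfection.

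On drug resistance, Section 10.2.2.3 plans to compare the two strategies. Section 6.3.2 tests confirmed virologic failures in Steps 2 and 3 and, "for a random subset of 20 patients 2 months after completing punctuated therapy", off-therapy samples. Section 10.2.2.3 adds patients whose virus rebounds during punctuated therapy. The virology sub-analysis (Appendix X, Analytic Design) repeats resistance testing at six months in all patients. For the immediate-treatment arm it says "repeat antiretroviral resistance testing will also be scheduled at the time of first positive VL specimen after discontinuation of ART".

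**The concern.** The power sentence covers each secondary comparison without qualification, so one clear exception is enough to make it wrong as written. Relapse is the obvious candidate, because the protocol itself forecasts very few events.

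If the sentence stays, a non-significant relapse comparison could be presented as adequately powered evidence that punctuated ARV therapy does not affect relapse. With 10 to 35 events the data could not carry that conclusion.

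**Working it through.** **Inputs.** Two-sided alpha of 0.05 ("alpha=0.05 (2 tailed), 1600 simulations", Section 10.1); 175 patients per arm; "allocation ratio of 1:1" (Section 5.2.2); 10 to 35 relapses in total (Section 10.2.2.2; 3% and 10% of 350 are 10.5 and 35). No secondary effect size is stated. The 35% used below is borrowed from HIV progression and read as a hazard ratio (HR) of 0.65. A halving is added as an assumed larger effect.

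**Reproducing the plan's own power.** There is no secondary calculation to reproduce. For the primary outcome I assumed exponential survival, 3-year uniform accrual, 5 years in total, HR 0.65 and 175 per arm. Ignoring dropout, power is 88.4% when half the reference arm progresses by 2 years (stated: 90%) and 79.3% when half progresses by 3 years (stated: 80%). With 5% dropout per year the figures are 86.0% and 76.0%. Reading the 35% effect as HR 0.65 is therefore reasonable.

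**Relapse, standard approximation.** Power = Φ(|ln HR|·√D/2 − 1.96), where D is total events.
- HR 0.65, D = 10: Φ(0.431 × 3.162/2 − 1.96) = Φ(−1.28) = 10%.
- HR 0.65, D = 35: Φ(0.431 × 5.916/2 − 1.96) = Φ(−0.69) = 25%.
- HR 0.50, D = 10: Φ(0.693 × 3.162/2 − 1.96) = Φ(−0.86) = 19%.
- HR 0.50, D = 35: Φ(0.693 × 5.916/2 − 1.96) = Φ(0.09) = 54%.
- HR giving 80% power = exp(−2 × 2.802/√D): 0.17 for D = 10 and 0.39 for D = 35.

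**Relapse, small-sample check.** The approximation is unreliable at 10 events. If k of the 10 fall in the punctuated arm, the log-rank statistic is close to (k − 5)/√2.5, which exceeds 1.96 in size only when k is 0, 1, 9 or 10. The chance that a given event falls in the punctuated arm is about HR/(1 + HR).
- HR 0.65: share 0.394, probability of an extreme split about 5%.
- HR 0.50: share 0.333, about 10%.
- HR 0.17: share 0.145, about 56%.
- HR 0.09: share 0.083, about 80%.

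A log-rank simulation with 175 per arm agrees: about 5% at HR 0.65, about 55% at HR 0.17 and about 80% at HR 0.09. With 35 events it gives about 76% at HR 0.39 and 82 to 83% at HR 0.36.

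**Relapse as a proportion, 175 per arm, normal approximation.**

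| Reference rate | Punctuated rate | Power |
|---|---|---|
| 10% | 6.5% | 22% |
| 10% | 5% | 43% |
| 3% | 1.95% | 9% |
| 3% | 1.5% | 16% |
| 3% | 0% | 64% |

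In the last row Fisher's exact test gives less. It needs at least 6 relapses against 0 (p = 0.030), and with 175 patients at 3% the chance of 6 or more is 43%. Detecting a 35% reduction with 80% power would take 969 patients per arm from a 10% reference rate and 3,436 from 3%.

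**Other secondary outcomes.** Section 1.1.2 cites paradoxical reactions in 36% with ARV therapy and 7% without. At 175 per arm that difference has power above 99%. Culture conversion reaches 80% power for absolute differences of about 11 to 15 points, if the reference rate lies between 30% and 80% (an assumption). For treatment failure and resistance the protocol gives no expected event numbers from which power could be computed.

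**The case against.** The strongest reply is that no secondary effect size is stated, so some effect always has 80% power and the sentence cannot strictly be refuted. That is fair against calling the claim flatly false, and nothing in the protocol allows a 61% reduction in relapse to be called implausible. But the same reply would rescue any sample size and would empty the sentence of content. At the protocol's one stated effect size, relapse falls far short. At the low end of its range, read as the reference rate, even complete prevention of relapse does not reach 80%.

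It can also be said that the trial was sized on the primary outcome, that Section 10.2.2.2 already plans a 95% confidence interval for the relapse rate ratio, and that nowhere does the protocol say a null result will be read as no effect. All three stand. They limit the consequence to interpretation, but they do not make the power statement correct.

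Two stronger readings are tempting and are not supported. One is that all secondary comparisons are underpowered; the paradoxical-reaction figures show otherwise. The other is that resistance is examined in only 20 patients. The 20 are one component, alongside virologic failures in Steps 2 and 3, rebounds on therapy, all patients at six months, and immediate-arm patients at first positive viral load after stopping. Nor is swapping the two-month sample for testing at first rebound a plain correction: one is taken at a fixed time and the other at an event, and both can coexist.

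**Conclusion.** The concern holds for relapse. The statement of 80% or greater power in each secondary comparison is wrong as written, because the protocol's own forecast of 10 to 35 relapses gives roughly 5 to 10% power (10 events) to 22 to 25% (35 events) at a 35% reduction, and at most about 54% at a halving. Power of 80% requires a hazard ratio of about 0.09 with 10 events or 0.36 to 0.39 with 35.

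These figures assume two-sided alpha of 0.05, 1:1 allocation and proportional hazards; the effect sizes are illustrative because the protocol states none for relapse. For treatment failure and resistance the 80% figure is unsupported, not disproved. Sample size, primary analysis and decision rules are unaffected.

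**What to change.** In Section 10.1, delete the sentence on secondary outcomes. Alternatively, replace it with a short list giving, for each secondary outcome, the assumed reference rate and the effect detectable with 80% power at 175 per arm. Use exact methods or simulation where events are few; the usual approximation would put the detectable hazard ratio for 10 relapses at 0.17, where actual power is only about 55%.

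In Section 10.2.2.2, state that the relapse comparison has low power, that it will be read from the estimate and its 95% confidence interval, and that a non-significant result is not evidence of no effect.

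For resistance, no change in sampling is called for. Sections 6.3.2 and 10.2.2.3 (random 20 at two months) and Appendix X (first positive viral load after stopping) should cross-refer, so that the full off-therapy testing is clear.

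The cost is wording and one short calculation, with no change to enrolment, visits or planned tests.

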## 10.2 Analytic Strategy

### **10.2.1 Descriptive Analysis**

A descriptive analysis will examine the distribution of continuous variables and the frequency histograms for categorical variables. In non-normal distributions, such as viral load, transformations will be used to normalize the data for statistical analysis. To assess the adequacy of randomization, baseline characteristics of the study groups will be compared using Wilcoxon rank sum test (students t-test for normal distributions) for continuous data or chi-square test for categorical data.76 Where the expected frequencies are small, exact methods may be used. Cumulative incidence of events (e.g., CD4 < 250, relapse TB) will be estimated as the number of events per population at risk at baseline for each treatment group; 95% confidence intervals will be determined using standard methods.77 Incidence density will be estimated as the number of new, or incident, events per 100 person-years of observation; appropriate 95% confidence intervals can be calculated.77 The clinical course of HIV infection will be characterized as the incidence density of opportunistic infections following the diagnosis of active TB. The relative risk of opportunistic infections in the treatment versus the reference groups will be estimated with 95% confidence intervals.77 Statistical analysis will be performed using SAS and S-Plus statistical packages.

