# Protocol Synopsis

| Hypothesis | *Punctuated* ARV therapy given during treatment of active TB will slow progression of HIV disease in TB patients with CD4+ cells > 350 cells/ μL. |
| --- | --- |
| Objectives | Primary objective:  To determine whether a punctuated six-month course of ARV therapy during treatment of active TB will delay HIV disease progression, as measured by time until CD4+ count falls below 250 cells/μL, the rate of decline in CD4+ cell counts, and incidence of opportunistic infections, among HIV-infected persons with active TB and CD4+ cell count above 350 cells/μL.  Secondary objectives:  a. To determine whether a punctuated six-month course of ARV therapy during treatment of active TB will improve the response to antituberculosis therapy, as measured by one and two month culture conversion, treatment failure, and relapse TB, among patients with active TB and CD4+ cell count above 350 cells/μL  b. To determine whether a punctuated six-month course of highly active ARV therapy is safe when given with antituberculosis therapy as measured by development of ARV drug resistance, toxicity and side effects, and paradoxical reactions. |
| Design | Phase III open-label, randomized, clinical trial. The study intervention will randomize, in a 1:1 manner, 350 eligible patients with active TB and a CD4+ count greater than 350 cells/μL to receive either immediate six-month punctuated course of ARV therapy (N = 175 patients) or delayed ARV therapy (N = 175 patients). |
| Population  & Sample Size | A total of 350 HIV-infected patients, male or female, 13 – 60 years of age, with active pulmonary TB and a CD4+ count greater than 350 cells/μL. |
| Experimental  Regimen | A total of six-months punctuated course of twice daily abacavir 300 mg/ lamivudine 150 mg/zidovudine 300 mg (as Trizivir®) concurrent with first line antituberculosis treatment |
| Comparative  Regimen | Antituberculosis treatment without six-months punctuated ARV therapy. Delayed ARV treatment will be started when the CD4+ count drops below 250 cells/μL. |
| Follow-up | Each patient will be followed for a minimum of 2 years from study enrollment. Total study duration is 5 years |
| Safety Evaluation | Serial medical history and physical examination, laboratory monitoring |
| Virologic Evaluation | Serial samples of plasma with quantitative measurements of viral load |
| Microbiological  Evaluation | Sputum semi-quantitative AFB smear and culture on solid media |

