### **7.3.3 Post-Study Intervention Follow-up (prior to study outcome)**

Each subject will undergo the following examinations during follow‑up after completion of the six-month ARV Intervention Phase (see Appendix I, Step 2). After completing the intervention phase, patients will be seen monthly until month 12, and then patients will be evaluated every 3 months for a minimum of two years. A patient may be followed up to a maximum of five years depending on the date of enrollment; patients will be evaluated every 4 months after the first three years.

1. Medical history and physical examination including weight, major TB and HIV-related signs and symptoms and primary study outcomes (Months 7, 8, 9, 10, 11, 12, 15, 18, 21, 24, 27, 30, 33, 36 and *every 4 months thereafter or as clinically indicated*)
2. New diagnoses and/or hospitalizations since the last study visit (Months 7, 8, 9, 10, 11, 12, 15, 18, 21, 24, 27, 30, 33, 36 and *every 4 months thereafter or as clinically indicated*)
3. Posterior-anterior chest X-ray (Months 12, 18, and as clinically indicated)
4. Adverse experiences survey (Months 7, 8, 9, 10, 11, 12, 15, 18, 21, 24, 27, 30, 33, 36 and *every 4 months thereafter or as clinically indicated*)
5. Sputum semi-quantitative AFB smear and culture on solid media X 2 (Months 12 and 18, *or as clinically indicated*)
6. MTB drug susceptibility (as clinically indicated)
7. Urine or serum -HCG pregnancy test (as clinically indicated)
8. CBC differential white blood cell and platelet count (Months 9, 12, 15, 18, 21, 24, 27, 30, 33, 36 and *every 4 months thereafter or as clinically indicated)*
9. Serum aspartate aminotransferase (AST), serum total bilirubin (as clinically indicated)
10. Serum Creatinine (as clinically indicated)
11. CD4+ lymphocyte counts (Months 9, 12, 15, 18, 21, 24, 27, 30, 33, 36 and *every 4 months thereafter or as clinically indicated*)
12. Plasma HIV RNA by Roche Amplicor (Months 9, 12, 18, 24, 30, 36, and then annually or as clinically indicated)
13. Quality of life assessment (months 12, 18, 24, 30 and 36)
14. Plasma storage (Months 9, 12, 18, 24, 30, 36 and *every 4 months thereafter, or as clinically indicated*)
15. PBMC storage/ immune function (Months 9 and 12, *or as clinically indicated*)
16. Store MTB isolate for DNA fingerprinting (All isolates from positive cultures of suspected relapse cases will be stored at -70° C for DNA finger printing with the patient’s initial isolate, as clinically indicated)

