The primary outcome for the study is HIV disease progression. This is defined as the time interval between enrollment and the development of one or more of the following endpoints, whichever occurs first: decline of CD4+ count < 250/µL, new AIDS-defining condition, or death. When a subject has met the criteria for primary outcome for CD4+ counts, the date for the first of 2 consecutive CD4+ counts will be used to mark failure time. The primary analysis of the study for each outcome will be to compare the failure-time distribution of the treated to the reference group. Separate failure-time distributions will be estimated for each treatment group using the Kaplan-Meier method78 and compared using the log-rank test.79 Stratified analysis will be performed for the primary outcome according to categories of baseline viral load.80 A Cox proportional hazards regression model81,82 will be developed to evaluate the effect of treatment on disease progression. In these analyses, the failure event will be HIV disease progression; subjects will be censored because of withdrawal during the study or at end of study. We will assess whether censoring is independent of study outcome as this is a fundamental assumption of survival analysis. In these regression models, observed event-free survival will be the dependent variable.

The basic Cox proportional hazards model for this analysis will be formulated as follows:

where h (t,X) is the observed hazard, h0 (t) is the baseline, unmeasured hazard for disease progression, β is the regression coefficient for treatment, ARV is the variable coding for immediate versus delayed ARV treatment (1 and 0, respectively), i the vector of regression coefficients for the covariates, Xi is the vector of covariates that may include time since treatment. This vector will contain known prognostic factors for HIV infection in Africa such as age, tuberculin skin test, baseline CD4+ count, hemoglobin, and performance status. This vector of covariates will also include the time period between initiating antituberculosis therapy and date of randomization to account for varying times in initiating antiretroviral therapy. The assumption of proportional hazards will be tested using graphical methods and formal statistical tests. If this assumption does not hold, then stratified Cox regression models will be developed, stratifying on the variable with non-proportional hazards.

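### Section 10.2.1 computes cumulative incidence as events over baseline N with no time point, although follow-up runs from 2 to 5 years; Section 10.2.2.2 uses a different estimator for relapse

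*Protocol*

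**What the plan says.** Section 10.2.1 sets a general rule. It opens with "Cumulative incidence of events (e.g., CD4 < 250, relapse TB" and continues that these "will be estimated as the number of events per population at risk at baseline for each treatment group". Confidence intervals of 95% are attached. No time horizon is given and censoring is not mentioned. The next sentence adds incidence density per 100 person-years, also with 95% intervals.

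Section 10.2.2.2 states for relapse: "The cumulative incidence of TB relapse will be estimated by group using Kaplan-Meier methods". It also counts the "number of relapses per 100 person-years of observation after completing antituberculous treatment according to ARV treatment group", so person-time for relapse starts at treatment completion and not at baseline.

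Section 10.2.2.1 handles the primary endpoint, of which CD4 below 250 is one component, by time-to-event methods: "Separate failure-time distributions will be estimated for each treatment group using the Kaplan-Meier method", and "subjects will be censored because of withdrawal during the study or at end of study".

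On the length of follow-up, the Synopsis says "Each patient will be followed for a minimum of 2 years from study enrollment. Total study duration is 5 years", and Section 7.3.3 says "A patient may be followed up to a maximum of five years depending on the date of enrollment".

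**The concern.** Events divided by baseline N estimates a risk only when everyone is observed over the same closed period. Here late enrollees are observed for about 2 years and early ones for up to 5. Anyone who drops out without an event stays in the denominator as if event-free for good. The result is an average over whatever follow-up happened to occur.

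For relapse there are two further problems. The same term is given a different estimator in Section 10.2.2.2, so one report could carry two unequal figures under one name. The baseline denominator also includes people who are not yet, or never, at risk, because Section 6.2.6 defines relapse as disease after a completed course of treatment.

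At stake are the absolute risks of CD4 decline and relapse, with their confidence intervals. Readers quote these figures and compare them across studies.

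**Working it through.** The protocol states no figure that depends on this rule, so there is nothing to reproduce. The check sizes the effect with the protocol's own design inputs.

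**Inputs**
- Figure 5 legend (Section 10.1): constant hazard, 3-year accrual, 5% dropout per year, and reference-arm progression of 50% by 2 years (A) or 50% by 3 years (B).
- Synopsis and Section 7.3.3: follow-up of 2 to 5 years.
- My assumptions: accrual is uniform, so administrative follow-up is uniform on 2 to 5 years, and dropout is exponential.

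**Formulas**
- Event hazard λ = ln 2 / median; dropout hazard η = −ln(1 − yearly dropout); h = λ + η.
- Expected events/N = (λ/h) × [1 − (e^(−2h) − e^(−5h)) / (3h)].
- True risk at time t = 1 − e^(−λt).

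**Scenario A, 5% dropout**
- λ = 0.3466, η = 0.0513, h = 0.3979, λ/h = 0.8711.
- e^(−2h) = 0.4512, e^(−5h) = 0.1368, 3h = 1.1936.
- Events/N = 0.8711 × [1 − 0.3144/1.1936] = 0.642.

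**Results for the reference arm**

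| Scenario | Events/N, no dropout | Events/N, 5% a year | Events/N, 10% a year (assumed) | True 2 y | True 3 y | True 5 y |
|---|---|---|---|---|---|---|
| A: 50% by 2 y | 68.9% | 64.2% | 59.7% | 50.0% | 64.6% | 82.3% |
| B: 50% by 3 y | 54.6% | 50.5% | 46.6% | 37.0% | 50.0% | 68.5% |

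The true risks do not change along a row, but the ratio does. In scenario A, the time at which the ratio equals the true risk is 3.37, 2.96 and 2.62 years for 0, 5 and 10% yearly dropout. There is no fixed horizon.

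**Does Kaplan-Meier cure it?** In 2,000 simulated arms of 175 with 5% dropout, scenario A gave mean Kaplan-Meier estimates of 0.499 at 2 years and 0.646 at 3 years (true 0.500 and 0.646), against 0.641 for events/N. Scenario B gave 0.371 and 0.501 (true 0.370 and 0.500), against 0.506.

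**Between arms.** Assume the 35% effect size means a hazard ratio of 0.65; the defining formula is not legible in the text at hand. In scenario A with 5% dropout in both arms, the ratio of crude figures is 0.496/0.642 = 0.77, and the ratio of true 3-year risks is 0.491/0.646 = 0.76. If dropout differed (5% against 10% a year, an assumption) with no treatment effect, the crude figures would be 64.2% and 59.7% although the true risks are equal.

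**Relapse.** Section 10.2.2.2 cites published relapse rates of 3 to 10%. Assume a constant relapse hazard, 1.5 to 4.5 years at risk after treatment and 5% yearly dropout. A crude 10% then corresponds to about 7.4% at 2 years and 10.9% at 3 years, and a crude 3% to 2.2% and 3.3%.

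**The case against.** The strongest reply is that nothing inferential rests on this sentence. It stands in a descriptive section. The primary outcome is compared by Kaplan-Meier, log-rank and Cox, with a stated check on independent censoring. Relapse is analysed by Kaplan-Meier, person-years and Cox. Section 10.2.1 itself gives incidence density, which allows for unequal follow-up. With similar dropout in the two arms, the between-arm ratio hardly moves. All of this stands and limits the weight of the point.

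It can also be said that the ratio lies within a point of the 3-year risk in both scenarios. That is true at 5% dropout but not at 0 or 10%, so it gives the figure no horizon. Incidence density is a separate quantity and does not repair the one labelled cumulative incidence.

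Two stronger readings are tempting. One is that Sections 10.2.1 and 10.2.2.2 flatly contradict each other, so that the relapse analysis cannot be carried out. The text does not go that far: a general descriptive rule and an aim-specific rule can both be executed, and nothing makes the first override the second. What remains is one label on two estimators. The other is that ignoring death as a competing event for relapse is part of the error. Kaplan-Meier with censoring at death is a choice the protocol makes in 10.2.2.2; a competing-risk estimator would be a refinement and would require changing that section too.

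**Conclusion.** The point holds as a minor defect in a stated rule. The quantity that Section 10.2.1 calls cumulative incidence has no defined time and depends on dropout: 68.9%, 64.2% and 59.7% in scenario A for 0, 5 and 10% a year, against a fixed 50.0% at 2 years and 64.6% at 3 years. For relapse it uses a different estimator from Section 10.2.2.2, though at the expected relapse rates the absolute gaps are only a few percentage points at most.

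The sizes rest on constant hazards, uniform accrual and exponential dropout; 10% dropout and any difference in dropout between arms are assumptions, not protocol figures. A reader might infer that the treatment comparison or the power is compromised. The documents do not support that: the harm is confined to descriptive absolute risks and their confidence intervals.

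**What to change.** In Section 10.2.1:
- Define cumulative incidence as a censoring-adjusted time-to-event estimate at stated times (for example 24 and 36 months) with its confidence interval, consistent with Sections 10.2.2.1 and 10.2.2.2.
- Start time at risk for relapse at completion of anti-TB treatment, as Section 10.2.2.2 already does for incidence density.
- Label any events/N figure a crude proportion.

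This is a wording change. It needs no new data and alters no test or sample size.

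Optional: if death is to be treated as a competing event for relapse, use a cumulative incidence function in place of Kaplan-Meier and change Section 10.2.2.2 to match. The two estimators should not be requested for the same figure.
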